## Abstract

**Background and Aims:**

The standard whole-colon tests used to investigate patients with symptoms of colorectal cancer are barium enema and colonoscopy. Colonoscopy is the reference test but is technically difficult, resource intensive, and associated with adverse events, especially in the elderly. Barium enema is safer but has reduced sensitivity for cancer. CT colonography ("virtual colonoscopy") is a newer alternative that may combine high sensitivity for cancer with safety and patient acceptability. The SIGGAR trial aims to determine the diagnostic efficacy, acceptability, and economic costs associated with this new technology.

**Methods:**

The SIGGAR trial is a multi-centre randomised comparison of CT colonography versus standard investigation (barium enema or colonoscopy), the latter determined by individual clinician preference. Diagnostic efficacy for colorectal cancer and colonic polyps measuring 1 cm or larger will be determined, as will the physical and psychological morbidity associated with each diagnostic test, the latter via questionnaires developed from qualitative interviews. The economic costs of making or excluding a diagnosis will be determined for each diagnostic test and information from the trial and other data from the literature will be used to populate models framed to summarise the health effects and costs of alternative approaches to detection of significant colonic neoplasia in patients of different ages, prior risks and preferences. This analysis will focus particularly on the frequency, clinical relevance, costs, and psychological and physical morbidity associated with detection of extracolonic lesions by CT colonography.

**Results:**

Recruitment commenced in March 2004 and at the time of writing (July 2007) 5025 patients have been randomised. A lower than expected prevalence of end-points in the barium enema sub-trial has caused an increase in sample size. In addition to the study protocol, we describe our approach to recruitment, notably the benefits of extensive piloting, the use of a sham-randomisation procedure, which was employed to determine whether centres interested in participating were likely to be effective in practice, and the provision of funding for dedicated sessions for a research nurse at each centre to devote specifically to this trial.

**Trial registration:**

Current Controlled Trials ISRCTN95152621

## Background

Computed tomographic colonography (CTC) is a relatively novel health technology used to examine the large bowel. Specifically, it combines helical CT scanning of the cleansed and distended colorectum with complex image rendering techniques, and is used primarily to detect colorectal neoplasia. CTC was first described in 1994 [1] and has been evaluated by several comparisons with colonoscopy, both single-centre [2,3] and multi-centre [4,5]. Meta-analysis of studies where patients have both CTC and colonoscopy suggests that CTC has high average sensitivity and specificity for diagnosis of colorectal neoplasia [6,7]. There are no randomised studies. Radiologists have repeatedly stressed a role in colorectal cancer screening, with claims that CTC combines excellent sensitivity for adenomatous polyps (the precursor of colorectal cancer) with safety and acceptability [8]. However, at the time of writing only a single published study has examined a representative sample [9] and the overwhelming majority of studies have been exclusively based on patients with symptoms suggestive of cancer. While these studies have made a case for screening by focussing on the detection of polyps, in reality polyps in these patients are serendipitous findings and not responsible for symptoms. The emphasis on polyps has obscured evidence that the sensitivity of CTC for colorectal cancer is possibly as high as colonoscopy and likely higher than barium enema, the standard tests currently used for diagnosis. A recent meta-analysis found an average sensitivity for cancer of 96% (95%CI, 91% to 99%) [6]. It follows that the role of CTC for diagnosis of symptomatic cancer deserves more attention.

Around 363,000 cases of colorectal cancer occur each year in the European Union and 148,000 in the USA [10]. It is important to make an early diagnosis because prognosis depends on tumour stage but local variations in clinical practice can delay this [11]. English patients with symptoms suggestive of colorectal cancer must be now be seen by a specialist within 2-weeks of referral by their general practitioner [12]. A "whole-colon" test is frequently requested to search for cancer but because the "suggestive symptoms" are non-specific and common in the general population (e.g. abdominal pain, change in bowel habit), most patients investigated do not have the disease. Colonoscopy is the most sensitive test but is expensive, resource intensive, technically difficult, and has a small but well-recognised morbidity and even mortality [13]. Furthermore, most patients investigated are elderly, the group most at risk from adverse events. Barium enema is safer than colonoscopy [14] but has reduced sensitivity [15], and interpretation skills are declining [16]. CTC is safer than colonoscopy [17,18] while being more sensitive than barium enema, and appears to be more acceptable to patients than either of the other tests [8]. CTC may also be performed by technicians and in principle the data could be read by computer-assistance [19], accelerating diagnosis and throughput.

The paragraphs above make the case that CTC may combine accurate diagnosis of colorectal cancer with safety and efficiency but CTC also presents the opportunity to investigate other intra-abdominal organs (unlike colonoscopy and barium enema) because these are included on the scan. Pathology outside the colon may sometimes underpin patients' symptoms and it is possible that CTC could have more diagnostic utility overall than tests restricted to the colorectum. However, characterisation of extra-colonic findings may also consume significant health-care resources investigating 'abnormalities' that ultimately prove insignificant: A recent study found that 116 (52%) of 225 symptomatic patients studied by CTC had one or more extracolonic findings, consuming £34,329 to pursue – a figure exceeding the original costs of CTC and effectively doubling investigation costs overall [20]. It is unknown how these costs, along with inconvenience, anxiety, morbidity and occasionally even mortality, are offset by the benefit to those with sub-clinical but potentially lethal diseases. CTC will also serendipitously detect significant adenomatous polyps (defined as 1 cm or lager in size) that are not responsible for symptoms but which, having been detected, will need endoscopic removal.

In this article we describe the protocol for the SIGGAR trial, a randomised comparison of CTC against either colonoscopy or barium enema. Participating radiologists are members of SIGGAR, the Royal College of Radiologists Special Interest Group in Gastrointestinal and Abdominal Radiology (now BSGAR, British Society of Gastrointestinal and Abdominal Radiology [21]). Research on this topic was commissioned by the UK Health Technology Assessment (HTA) programme in 2002, who are funding the study (proposal 02/02/01).

### Study objectives

• To compare the detection rates and diagnostic sensitivity for significant colorectal neoplasia of CTC versus barium enema and CTC versus colonoscopy.

• To examine psychological and physical morbidity associated with each diagnostic pathway.

• To determine costs of diagnosis associated with each diagnostic pathway.

• To determine the frequency, clinical relevance, economic costs, and psychological and physical morbidity associated with detection of extracolonic lesions by CTC.

• To use data accumulated from the trial to populate models framed to summarise the health effects and costs of alternative approaches to detection of significant colonic neoplasia in patients of different ages, prior risks and preferences.

Diagnostic pathway is defined by the procedure to which the patient is initially randomised, recognising that some patients will undergo more than one of the tests ('conversion'), for example due to technical failure or to confirm the result of the initial test.

## Design and methods

### General

The SIGGAR trial comprises two parallel prospective randomised multicentre studies, each with a 2:1 randomisation in favour of the 'default' whole-colon examination (Figure 1). One sub-trial compares CTC against colonoscopy and the other CTC against barium enema. Recruitment commenced April 2004.

**Figure 1 F1:**
[figure not shown]
Flow chart of patient recruitment to each sub-trial with sample size for each group randomised.

### Inclusion/exclusion criteria

Eligible patients are aged 55 years or older, able to give informed consent, with symptoms or signs considered suggestive of colorectal cancer by the referring physician (e.g. change in bowel habit, rectal bleeding, abdominal pain, anaemia). A decision to perform a "whole-colon" examination to diagnose/exclude colorectal cancer will have been taken by the clinician-in-charge and patients must therefore be fit to undergo full bowel preparation. Patients with a known genetic predisposition to cancer, inflammatory bowel disease, or who are being followed-up for colorectal cancer are excluded. They must have had no "whole-colon" examination in the past six months.

Participating centres must have an established and efficient fast-track clinical referral system for managing patients referred with symptoms suggestive of colorectal cancer, with a throughput sufficient to recruit at least 18 patients a month. Centres must also be able to satisfy technical stipulations for the diagnostic interventions (see section below). Participating centres were chosen fro those interested in participating via a sham-randomisation procedure (see Discussion).

### Ethical arrangements and consent

The SIGGAR trial achieved multi-centre ethical committee (MREC) approval in January 2004 and is being conducted in accordance with Medical Research Council guidelines for good clinical practice in clinical trials and the Research Governance Framework. Informed consent is a prerequisite. The trial is supervised by an independent data monitoring committee (DMC) and trial steering committee (TSC) (see Acknowledgements).

### Randomisation

Basic demographic and clinical information is collected and patients registered at the time they are judged potentially eligible for randomisation, usually by inspection of referral forms/clinic letters in the days just prior to attendance. Eligible, registered patients are then randomised after agreement by the lead clinician and patient but data relating to registered patients who are ultimately not randomised are retained along with the reason for non-randomisation, so that external validity can be judged and estimates of generalisability made once the data are known.

Randomisation is performed centrally, at the trial office. Patients are randomised 2:1 in favour of the default diagnostic test (i.e. colonoscopy or barium enema). On the advice of the DMC, details of stratification/blocks are confidential since it is theoretically possible to predict allocation for some patients if past allocation and block site is known.

### Diagnostic interventions

#### 1. CT colonography

CT colonography has undergone rapid technological evolution since first described, which continues at the time of writing. There have been particular advances in visualisation software. Because recruitment will take several years, the protocol allows investigators to adopt advances during the course of the trial so that findings are as up to data as possible. The protocol for CTC is based on expert consensus where this exists [22]. For example, multi-detector row scanners are mandatory and patients must undergo full bowel preparation, and both prone and supine scanning at a minimum collimation of 2.5 mm. Where no consensus exists, for example administration of intravenous contrast and spasmolytic [23], local investigators have freedom to choose in line with their personal preference, which reflects normal clinical practice and enhances generalisability. Interpretation software has been provided (Voxar, Barco, [name], Edinburgh, United Kingdom, and V3D, Viatronix Inc, Stony Brook, NY), but local investigators are free to use other commercially available platforms according to their preference. Observers may use 2-D or 3-D reading, or any combination of the two, reflecting individual preference in normal clinical practice. Observers may report any colonic or extra-colonic finding that they feel may explain patients' symptoms or which they consider potentially relevant, in line with personal diagnostic thresholds. Interpretation is limited to consultant radiologists with a demonstrable subspecialist interest in gastrointestinal imaging (those attending the gastrointestinal multi-disciplinary team meetings for example), reflecting established practice for investigation of symptomatic patients. All have previous experience of CTC that has been supplemented with a two-day training course for the purposes of the study. Trial centres encompass both teaching and district general hospitals to enhance generalisability.

#### 2. Barium enema

Barium enema examinations are performed after full bowel preparation, using best current practice; i.e. digital fluoroscopy (512 matrix minimum) of the double-contrasted colorectum to the caecum, supplemented by overcouch decubitus films. A spasmolytic and carbon dioxide is used. Examinations are performed by either radiologists with a subspecialty interest in gastrointestinal radiology or radiographic technicians fully trained in barium enema procedures, reflecting conventional practice. Enemas are reported by radiologists with a subspecialty interest in gastrointestinal radiology.

#### 3. Colonoscopy

Colonoscopy is performed by experienced colonoscopists, either physicians or surgeons who have satisfied stipulations on training made by the joint advisory group on gastrointestinal endoscopy (JAG) [24]. Modern video-endoscopes are used and sedation and analgesia administered when judged clinically necessary in each individual case. Colonoscopy to the caecum is intended initially in all cases.

Datasheets for each diagnostic procedure are completed by practitioners and detail clinical findings, procedural information (quality of bowel preparation, completeness, difficulty, diagnostic confidence, for example), any adverse events, and data necessary to calculate resource consumption subsequently.

We will obtain data for diagnosis of colorectal cancer for randomised patients from the Office for National Statistics (ONS) so that we have a denominator for calculation of sensitivity in addition to detection rates by each diagnostic test.

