### Outcome measures

#### Primary outcome measures

1. **CTC vs barium enema**. Detection rates and diagnostic sensitivity of significant colonic neoplasia by each test

2. **CTC vs colonoscopy**. Requirement for additional tests needed to diagnose or exclude significant neoplasia.

Significant colorectal neoplasia is defined as cancer or polyps 1 cm or larger. Such polyps may have a clinical consequence for patients even if they are not the cause of symptoms. We do not focus on detection rates in the colonoscopy sub-trial because available evidence suggests that colonoscopy and CT have equivalent sensitivity for significant colorectal neoplasia.

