### Analysis

The two sub-trials will be analysed as two separate case-control studies. In each sub-trial, cases and controls will be compared regarding covariates, including age, sex and centre, using chi-squared or Fisher's exact test for categorical variables and an unpaired t-test for continuous variables. The primary outcomes will be analysed using multivariable logistic regression with study group as the primary explanatory variable and adjustment for other covariates, including age, sex and centre. Centre will be considered as a random variable and the analysis will be clustered on centre. Secondary outcomes will be analysed using poisson regression for counts and logistic regression for proportions with the same explanatory variables. The data will be analysed in Stata 9.2 and variables will be considered significant at the 5% level.

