### Sample size assumptions

It is important to recognise that in a trial such as SIGGAR, patients do not contribute to the primary end-point unless they ultimately prove to have the target disease. Centres with a low prevalence of cancer are therefore not as effective as their recruitment suggests at first glance: It is well recognised that the prevalence of disease in trials is lower than would be expected normally. In such a situation it is important that the investigators and Data Monitoring Committee (DMC) continually reassess recruitment in the light of the prevalence of abnormality. An interim analysis carried out for the Trial Steering Committee Meeting in December 2005, at a time when 1237 patients had been randomised, noted that the prevalence of abnormality was 7% overall, compared with the 10% expected prior to the trial starting. Thus the trial had accrued fewer end-points than anticipated. The prevalence of abnormality also varied between sub-trials, being 12% in the colonoscopy sub-trial but only 5% in the barium enema sub-trial. Furthermore, although we had anticipated a 50:50 split between the two sub-trials, 862 (69.7%) had been recruited to the barium enema sub-trial (where the prevalence of abnormality is lowest), and only 375 to the colonoscopy sub-trial. A request for extension was made successfully, pointing out the need to increase the numbers in the barium enema sub-trial above the original sample size estimate while also increasing the rate of recruitment to the colonoscopy sub-trial. Power was also reduced from 90% to the more conventional 80% overall. The original sample size of 4320 (2160 randomised in each sub-trial) is now 4832, with 3402 patients needed in the barium enema sub-trial and 1430 in the colonoscopy sub-trial to acquire sufficient end-points, taking into account the difference in disease prevalence between the two sub-trials. At the time of writing 5025 patients have been recruited and the trial is in a position to close assuming that sufficient end-points have been accrued.

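### The logistic model set for every primary outcome may give no finite odds ratio or Wald interval for diagnostic sensitivity, because the CTC arm has a material chance of containing no missed cancer

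*Protocol article*

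**What the plan says.** All references are to the protocol article.

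- **Primary outcome measures.** For CTC against barium enema the primary outcome is "Detection rates and diagnostic sensitivity of significant colonic neoplasia by each test". The target is wider than cancer: "Significant colorectal neoplasia is defined as cancer or polyps 1 cm or larger".
- **Diagnostic interventions, 3. Colonoscopy.** Colorectal cancer diagnoses among randomised patients are to be obtained from the Office for National Statistics, "so that we have a denominator for calculation of sensitivity in addition to detection rates by each diagnostic test". No equivalent outside source is described for polyps.
- **Analysis.** "The primary outcomes will be analysed using multivariable logistic regression with study group as the primary explanatory variable", with adjustment for covariates including age and sex. On centre: "Centre will be considered as a random variable and the analysis will be clustered on centre". Fisher's exact test appears in this section only for comparing covariates between the groups.
- **Background.** A meta-analysis is cited for an average CTC sensitivity for cancer of 96% (95% CI 91% to 99%).
- **Sample size, 1. Diagnostic yield.** The revised calculation uses detection rates of 7.5% (CTC) and 5% (barium enema), 2:1 allocation, 80% power and two-sided alpha 0.05, giving 3402 patients.
- **Discussion, Sample size assumptions.** At the interim look the prevalence of abnormality differed between sub-trials, "being 12% in the colonoscopy sub-trial but only 5% in the barium enema sub-trial".

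**The concern.** One model is prescribed for two quantities with very different denominators. A detection rate is a proportion of all randomised patients, over a thousand in the CTC arm, with about 85 CTC events planned (1134 × 7.5%). Sensitivity is a proportion of patients who have the disease. As far as missed disease can be established independently, those are the registry cancers: tens of patients per arm.

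Within that small group, the contrast between arms is carried by the missed cancers. If CTC is as sensitive as the article's own citation suggests, the CTC arm will have very few. If it has none and barium enema has some, study group separates the data. The likelihood then keeps rising as the log odds ratio grows, so there is no finite maximum-likelihood estimate and no usable Wald interval. Where one or two misses do occur, a model that also carries age, sex and a random centre effect rests on almost no CTC events.

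At stake is whether one of this sub-trial's two primary measures can be reported with an effect size and an interval. The risk rises with the sensitivity of CTC.

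**Working it through.** **1. The plan's sample size.** Let p1 = 0.075, p2 = 0.05, ratio r = 2, pooled p = (0.075 + 2 × 0.05)/3 = 0.05833.

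- Uncorrected CTC arm: [1.96 × √(3 × 0.05833 × 0.94167) + 0.8416 × √(2 × 0.075 × 0.925 + 0.05 × 0.95)]² / (2 × 0.025²) = 1.1589² / 0.00125, about 1075 (3225 in all).
- Continuity-corrected: (n/4) × [1 + √(1 + 2(r + 1)/(n r × 0.025))]² = 1134.
- Total: 3 × 1134 = **3402**, an exact match. The CTC arm is therefore 1134.

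**2. Cancers in the CTC arm (m).** The article does not give the share of abnormalities that are cancers, so it is an assumption, varied from 25% to 100%. At the interim 5%, 1134 × 0.05 = 57 abnormalities.

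**3. Chance of no CTC miss.** With sensitivity s the same for all patients and independent results, P(no miss) = s^m and expected misses = m(1 − s). At s = 0.96:

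| Prevalence | Cancer share | m | Expected misses | P(no miss) |
|---|---|---|---|---|
| 5% | 25% | 14 | 0.6 | 56% |
| 5% | 50% | 28 | 1.1 | 32% |
| 5% | 75% | 43 | 1.7 | 17% |
| 5% | 100% | 57 | 2.3 | 10% |
| 7.5% | 25% | 21 | 0.8 | 42% |
| 7.5% | 50% | 43 | 1.7 | 17% |
| 7.5% | 100% | 85 | 3.4 | 3% |

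The chance exceeds one half only when m is about 17 or fewer (ln 0.5 / ln 0.96 = 16.98). Across the cited confidence limits at m = 28, it is 7% for s = 0.91 and 75% for s = 0.99.

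**4. What the model does with a zero cell.** Take an illustrative table (assumed counts) with 0 of 28 cancers missed by CTC and 12 of 57 by barium enema. In a logistic fit with study group and simulated age and sex, the log odds ratio is 10.2 (SE 37) after 10 iterations and 22.2 (SE about 14,756) after 25. It is still diverging, and the standard error is meaningless.

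**5. What survives on the same table.**

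- Likelihood-ratio test for study group, without covariates: chi-squared 10.54 on 1 df, p = 0.001. Fisher's exact test: p = 0.007.
- Wilson 95% intervals for sensitivity: CTC 28/28, 87.9% to 100%; barium enema 45/57 = 78.9%, 66.7% to 87.5%.
- Newcombe interval for the difference of 21.1 points: lower 0.211 − √[(1 − 0.879)² + (0.875 − 0.789)²] = 0.062; upper 0.211 + √[0² + (0.789 − 0.667)²] = 0.333. That is 6.2 to 33.3 points.

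The data can support an estimate and interval; the prescribed model cannot deliver them.

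**The case against.** **The test need not fail.** A reader might infer that a real CTC advantage would be reported as not significant. The article does not support this, because the Analysis section names no Wald test. The likelihood-ratio test from the same model still works with a zero cell. Enumerated without covariates, with 17, 28 or 45 CTC cancers (shares of 30%, 50% and 80%) and barium enema sensitivity of 64% (96% × 5/7.5), its power is 85%, 97% and 99.9%, against 76%, 95% and 99.8% for Fisher's test. So no loss of power is shown. This part of the objection stands.

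**It may not happen often.** A reader might also infer that a CTC arm without misses is the usual case. That depends on a cancer count the article does not give. The interim 5% may also be what the tests found rather than true prevalence. If so, at sensitivities of 96% and 64% the pooled sensitivity is (96 + 2 × 64)/3 = 74.7% and true prevalence is 5%/0.747 = 6.7%. At a 50% share that gives m = 38 and a 21% chance of no miss, rather than 32%. This stands too: the chance is material, but no single figure is established.

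**The target is wider than cancer.** The primary definition includes polyps of at least 1 cm, while the 96% and the registry denominator concern cancer alone. That is correct, and it limits the point to the part of sensitivity with independent ascertainment.

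**The full protocol or SAP may name a fallback.** It may. But the point is not a missing detail: the article states a method for all primary outcomes, and that method is poorly matched to one of them.

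**Conclusion.** The point holds as a mismatch between a stated model and one of the two primary measures of the barium enema sub-trial. With 1134 CTC patients, 5% abnormal, cancers making up 25% to 100% of abnormalities and 96% CTC sensitivity, the chance that the model has no finite odds ratio or Wald interval is 56% down to 10%. With the 3562 patients already randomised (about 1187 in the CTC arm) it is similar: m = 15 to 59, or 54% to 9%. Higher true prevalence lowers it, to about 3% if all lesions at 7.5% were cancers.

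The size rests on the assumed cancer share, independent results and a common sensitivity. The loss is the estimate and its interval. Detection rates, the measure on which this sub-trial was sized, are unaffected, as is the conversion-rate outcome in the colonoscopy sub-trial.

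**What to change.** Keep the multivariable logistic model for detection and conversion rates. For sensitivity, add wording such as:

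*Sensitivity for colorectal cancer will be reported as the proportion of registry-confirmed cancers detected in each arm, with an exact or Wilson 95% interval, and as the difference between arms with a Newcombe score interval; this is the main result. An adjusted analysis will use Firth-penalised logistic regression on study group, age and sex, with a penalised likelihood-ratio test and profile-likelihood interval.*

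The text should also say that this analysis covers cancer, which is only part of the wider primary target.

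The cost is a few sentences. The downside is that the main sensitivity comparison is not adjusted for centre, age and sex, and the penalised model leaves centre out. Settling this before outcomes are known avoids changing the method for a primary outcome after seeing a zero cell.
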